### Study population

Study phase 2 will involve the following inclusion criteria: LD caregivers of patients ≥ 18 years old, suffering from a malignant or non-malignant life-limiting chronic disease, including HIV/AIDS (ICD-10: B20–24), a malignant neoplasm (IDC-10: C00–97), a chronic heart condition (ICD 10: I00–I52), chronic kidney disease (ICD-10: N18, N28, I12, I13), chronic liver disease (ICD-10: K70–77), chronic respiratory system disease (ICD-10: J40–47, J96, E84), a disease of the nervous system (ICD-10: G10, G12, G20, G23, G35, G71), dementia or Alzheimer disease (ICD-10: F00, F01, F03, G30) and/or senility (ICD-10: R54). LD caregivers must be ≥ 18 years old and unable to have daily face-to-face contact with the patient due to geographical distance (other place of residence) [16] and they must perceive themselves as an LD caregiver. All individuals who meet these criteria, irrespective of sex and ethnic background, may participate. LD caregivers who fulfil the inclusion criteria will be invited to participate in the individual interviews.

LD caregivers will be recruited via: [1] established contacts with general practitioners, palliative care units (incl. palliative care consultation services), hospices and specialized palliative home care teams in the Hanover region; and 2) public relations (e.g. press releases, notices sent to self-help groups). If recruitment progresses slowly in the Hanover region, outreach to further palliative care units (e.g. Hamburg), home care teams and general practitioners will be used to expand the recruitment pool. This strategy has successfully been applied in the “Dy@EoL” project [56].

The advantage of the dual recruitment strategy is that it is likely to reach both relatives of patients in early palliative care (e.g. via general practitioners providing general palliative care to patients at home) and relatives of patients in a very advanced stage of disease (e.g. via hospices). The project team will evaluate the study eligibility of all patients and their family caregivers in collaboration with the relevant multi-professional palliative care teams/general practitioners.

All participating LD caregivers will be interviewed individually. Those who are living in Germany will be offered the choice between face-to-face and telephone interviews and (in the case of face-to-face interviews) allowed to choose the interview location. Interview rooms will be available at the Institute for General Practice and Palliative Care; however, on request, project team members will visit LD caregivers at a private, primary or palliative care environment of their choosing. Interviews at neutral locations will also be facilitated. Participants will be reimbursed for any travel expenses to and from the interview location, as well as for parking costs. Members of transnational families and significant others living abroad and providing LD care can participate in the study if they consent to a telephone interview. In the event that patients receive support from more than one LD caregiver, all involved LD caregivers will be invited to participate. If a participating LD caregiver experiences significant discomfort or distress during the interview, the interview will be terminated and, if agreed by the participant, continued at a later time. All LD caregivers will provide written informed consent to participate in the project, after having received comprehensive oral and written information about the nature, content and aim of the study, and study participation.

### Inclusion, exclusion and termination criteria

All participating LD caregivers whose mother tongue is not German will be offered an interpreter. Each interpreter will sign a confidentiality agreement prior to the interview. Consent forms and project information sheets will be translated for all relevant research participants. Prior to the interview, interpreters will be extensively briefed on the research topic and a research team member will review the interview questions with them and discuss specific situations that might arise.

Exclusion criteria for LD caregivers will include: (1) cognitive impairment (e.g. dementia), (2) lack of consent to participate and (3) death of the patient prior to interview. Termination criteria will comprise: (1) significant emotional distress during the interview, (2) insufficient cognitive skills to answer the interview questions and (3) withdrawal of project participation.

### Field access and feasibility

The Institute for General Practice and Palliative Care belongs to a network of 250 academic teaching practices that contribute to research and education. Moreover, the Institute for General Practice and Palliative Care currently collaborates with regional and national palliative care units, hospices and specialized palliative home care teams for the purpose of participant recruitment to several palliative care research projects. In this study, general practitioners and members of the multi-disciplinary palliative care teams will evaluate, in close cooperation with the project team, whether a patient is receiving LDC from a family member, in order to assess potential study eligibility. Eligible LD caregivers will be approached by a project team member, who will invite them to participate in an individual face-to-face interview.

Generally, family members report benefits from participating in end-of-life care research, and show high willingness to participate [63–65]. Hence, the anticipated recruitment of 30–35 LD caregivers is feasible. Participants will be asked about their motivation to participate in the project and eligible participants who decline participation will be asked for their reasons. The participation rate and reasons for (non-)participation will be recorded and entered into IBM SPSS Statistics. If necessary, these recruitment data will be used to enhance the recruitment strategy.

### Advisory board

To gain further valuable input and to differentiate the findings from research on other groups and contexts (e.g. local caregivers to end-of-life patients), a high quality multi-faceted advisory board will support the research and project team throughout the project lifetime. Specifically, the advisory board will support the project team in: (1) reviewing the project design and methodology, (2) contributing to the development of the semi-structured interview guide and socio-demographic quantitative assessment instrument, (3) refining the recruitment strategy (incl. the involvement of interpreters), (4) reflecting on any content and methodological issues emerging from the data collection and (5) finalizing the recommendations for support interventions, in collaboration with the Delphi study. Furthermore, the advisory board will provide constructive advice on the recruitment of under-represented groups.

The board will enhance the relevance, quality and acceptance of the research project by co-shaping the project and advising on the prioritization of the results [66]. It will operate via three in-person meetings (project months 4, 8 and 21, respectively) and one Delphi study (project month 23). The board will include researchers on end-of-life care, with expertise in the research methods (e.g. qualitative interviewing of vulnerable groups, recruitment of participants with immigrant background); practitioners of direct end-of-life care involving patients and caregivers, who will be particularly called on to contribute to the third advisory board meeting and the Delphi study, on the basis of their valuable insight into the practical relevance and feasibility of the recommendations for support interventions; representatives from recruitment partners and caring professions (i.e. physicians, nurses, case managers, counsellors, social workers, psychologists, psycho-oncologists); researchers with expertise in working with interpreters to engage with more diverse participants; and patient representatives.

### Risk to subjects

This is a low-risk project, involving no interventions that are likely to cause a side effect. Due to the narrative nature of the project, participating LD caregivers may experience discomfort (e.g. anger or sadness) when discussing their loved one’s life-limiting illness/death and their own grief experience. However, studies using comparable designs have reported a low participant burden [67–69]. Upon request, resources will be provided to participants to counter any discomfort they may feel, and referrals will be made to counselling services, where appropriate. The principal investigator will be present or accessible during all interviews. It is not anticipated that suicidality will emerge within this project; however, if this should arise, the principal investigator will determine whether additional safety precautions are needed.

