In general, the challenges experienced by LD caregivers may be exacerbated by work commitments, with serious implications for caregivers’ health, social isolation and finances [3, 7, 9, 10, 22, 23]. For instance, it is well documented that cancer and other life-threatening illnesses tend to severely affect the health and well-being of family members [24–27]. Family caregivers may also experience stress when breaking bad news to other family members, and they may suffer mental health problems if they are unprepared for the death of their loved one [22, 23, 28]. Although LD caregivers experience burdens similar to those expressed by local caregivers, LD caregivers describe additional burdens unique to their LDC situation, underscoring the particular difficulties of managing distance in this context [3]. Furthermore, LD caregivers experience emotional suffering and report feelings of sadness, helplessness, anger, grief, frustration, anxiety and guilt [3, 12, 20, 29, 30], due to their geographical distance from their loved one at the end of life, which prevents them from getting to their relative quickly. Indeed, they often worry about their ability to make a timely arrival in the event of a crisis [20]. LD caregivers may express a wish to do more for their family member [3, 15, 31], experience uncertainty about the ideal visiting time and struggle with the social expectation that close kin—particularly children—are expected to visit end-of-life patients in person [11]. Moreover, LD caregivers may struggle to cover travel costs and take extended leave from work without pay [11]. Refugees face the additional obstacle of being unable to leave the country due to restrictions linked to their immigration status [11]. Finally, given their reliance on second-hand information, LD caregivers often express a need for more information about their loved one’s disease, therapy and prognosis [20]. However, LD caregivers also describe positive aspects of caring from a distance, such as an appreciation of their ability to contribute to their relative’s care [29]. In Mazanec’s [20] study, adult child caregivers experienced an intensification of their relationship with their ill parent, due to their numerous phone conversations. Finally, LD caregivers express a perceived benefit of not being exposed to the terminal illness experience every day, but being able to step away and engage in leisure activities [12, 20].

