## Study aims

The project will explicitly address caregivers, as these figures often put aside their own needs to focus on providing support for a loved one [41]. The overarching goal of the project will be to detail the specifics of LDC at the end of life in Germany, outlining the ways in which distance shapes end-of-life caregiving and identifying the needs of end-of-life LD caregivers. More specifically, the project will seek to uncover caregivers’ perceptions and experiences of LDC, and how these might vary amongst caregivers from different cultural backgrounds. Ideas of what “good care” means at the end of life will also be explored, considering relevant aspects of diversity.

The two core research questions will be: (1) How do caregivers experience LDC for a relative at the end of life (in terms of, e.g., the caregiver’s life, health, and well-being; emotional, physical and financial burdens; and interpersonal conflict with the care recipient and/or other family members)? and (2) What are the specific (support) needs of end-of-life LD caregivers and what support do they desire and need, both for themselves and for the care recipient? Accordingly, the project will: (i) describe the specifics of LDC at the end of life and (ii) recommend support interventions for LD caregivers.

This exploratory research project will generate and disseminate scientific knowledge on LDC based on LD caregivers’ own experiences, understandings and perceived needs, and thereby fill knowledge gaps in the literature and contribute to opening new directions for LD caregiver research. Furthermore, the project will aim at producing knowledge to inform society and policy makers, at both local and national levels, regarding support for family caregivers of end-of-life patients. Such knowledge is critically needed, given the increasing number of individuals living at a geographical distance from their family. As this trend intensifies, traditional models of care within families will be challenged, shedding light on novel caregiving issues that will need to be addressed through social and health policy.

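### Support resources for foreseen interview distress depend on the participant asking, and stopping an interview for distress is not linked to any offer of support

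*Protocol article*

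**What the plan says.** Under Risk to subjects, the protocol article classes the project as low-risk but foresees feelings such as anger or sadness when caregivers talk about illness, death and grief. It then states two provisions in one sentence: "Upon request, resources will be provided to participants to counter any discomfort they may feel", and "referrals will be made to counselling services, where appropriate". It adds that "The principal investigator will be present or accessible during all interviews". Suicidality is not anticipated, but if it arises the principal investigator decides on precautions.

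Two other sections deal with distress in the interview. Under Study population, if a caregiver becomes significantly distressed, "the interview will be terminated and, if agreed by the participant, continued at a later time". Under Inclusion, exclusion and termination criteria, significant emotional distress is listed as a reason to terminate. Neither section mentions support at that point.

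The Study aims section explains why the project addresses caregivers at all: "these figures often put aside their own needs to focus on providing support for a loved one".

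**The concern.** A trigger that depends on the participant's request works only if distressed people ask. The article gives its own reason to doubt that for this group. The tension lies between a rule the article states and a premise it states, so it does not depend on anything the article leaves out.

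The most exposed participant is one whose interview is stopped for distress, who asks for nothing and who does not want to resume. The team has seen the distress and acted on it, but the sections that govern stopping lead only to a possible continuation, which serves data collection. Whether that person receives resources then rests on a referral judged appropriate, and the article does not say who makes that judgement or when.

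At stake is participant protection. No research question, analysis or conclusion changes.

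**Working it through.** No figure in the plan bears on this point and no statistical formula is involved. The check is a side-by-side reading of the provisions and of what sets each one in motion.

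| Provision | Section | What triggers it |
|---|---|---|
| Support resources | Risk to subjects | The participant's request |
| Counselling referral | Risk to subjects | Appropriateness; who judges, and when, is not stated |
| Stopping the interview | Study population; Inclusion, exclusion and termination criteria | Significant distress, acted on by the team |
| Continuing later | Study population | The participant's agreement |
| Precautions for suicidality | Risk to subjects | The principal investigator's decision |

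1. **Resources.** The request is the only trigger stated.

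2. **Referral.** The opening words about a request may or may not govern the second half of the sentence. Read separately, referral is a team judgement. A request-only rule is therefore established for resources and not for referral.

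3. **Stopping.** The team initiates it, so the plan is not wholly passive. Neither section that provides for stopping connects it to resources or referral.

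4. **Premise.** The Study aims statement is qualified by the word *often*. It makes failure to ask plausible for some participants, not certain for any.

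5. **Setting.** Under Study population, caregivers abroad take part by telephone and those in Germany may choose it. Under Inclusion, exclusion and termination criteria, those whose mother tongue is not German are offered an interpreter. My inference, not a statement of the article, is that unvoiced distress is harder to notice by telephone and that asking for help through a third person is harder.

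6. **Size.** The expected number leaving without resources would be

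   number missed = N × d × (1 − a) × (1 − s),

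   where N is the number interviewed, d the share distressed, a the share of those who ask, and s the share of the rest reached by the team unasked. The article gives only N, about 30–35. It gives no d, a or s, so the product cannot be evaluated.

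**The case against.** The strongest reply is that the team does act unasked. It stops interviews, it may refer, and it responds to suicidality. This stands, and it rules out the reading that all support depends on a request.

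Second, this is a condensed article. A distress procedure or support sheet may sit in the full protocol or the participant information, so silence about a later welfare check is no finding. This also stands. A reader might infer that support ends with the interview, or that participants are never contacted again. The article says neither: the sentence on resources and referral has no time limit, an interrupted interview may be resumed, and the Discussion promises a results letter after publication. The request trigger is different, because it is written down.

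Third, Phase 2 has every interview cover burdens and support needs, so needs are elicited from everyone. That lowers the chance that distress goes unnoticed. It does not settle the matter, because those questions gather data on caregiving and are not tied to an offer of resources.

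Two further inferences are tempting and fail:

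- The background says of family caregivers that "they may suffer mental health problems if they are unprepared for the death of their loved one". Since caregivers whose patient has died before the interview are excluded, a reader might conclude that the main risk falls after it and goes unobserved. But that is a burden of caregiving and bereavement, not harm caused by one interview.
- A reader might also say that the study cannot support its low-risk label from its own data. The label is a prospective classification resting on the absence of risky interventions and on comparable studies; it is not a claim the study sets out to test.

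Finally, one may call a universal list a matter of preference, since the two statements do not strictly contradict each other. They do not, but the request rule suits the described population poorly and the alternative is nearly free.

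**Conclusion.** The point holds in a limited form. The stated trigger for support resources fits badly with the article's own description of these caregivers, and stopping for distress is not joined to an offer of support. Some distressed participants who do not ask **may** leave without resources. That they **will** be missed is more than the text supports.

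The size cannot be given. All of the roughly 30–35 caregivers are exposed to the foreseen discomfort, but any count of those missed would rest on assumed rates.

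The conclusion assumes that the full protocol carries the same request rule as the article. If participants already receive a support list with their information sheet, the remedy reduces to saying so. This is a cheap improvement to participant protection.

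**What to change.** - **Risk to subjects:** replace provision on request with a written list of support resources given to every participant, translated alongside the consent forms and information sheets that are already to be translated.
- **Study population, and Inclusion, exclusion and termination criteria:** state that when an interview is stopped for distress, the team actively offers those resources, whether or not the interview is resumed.
- **Referral:** add a clause saying who judges when referral is appropriate.

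Which support is clinically suitable stays with the investigator. Routine follow-up of all participants is not asked for. The cost is about one page of extra translated material and brief added contact for the few participants whose interview is stopped, part of which overlaps with asking whether they wish to continue.

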### Data handling: protection of participants’ privacy, data confidentiality and archiving

Confidentiality will be maintained through the use of identification numbers to label all audio recordings and transcripts. A document containing participant names and identification numbers will be maintained separately from the audio recordings and transcripts. There will be no link between participants’ identifying information and their identification number. Consent forms will be stored separately from the data, in a locked filing cabinet. Digital files will be encrypted and stored on password protected desktop computers. Access to participant files will be limited to the principal investigator and the project team. When the results of the research are published or discussed at conferences, no participant identities will be revealed.

### Dissemination of the research results

Once the data analysis is complete and written up, articles will be published in peer-reviewed open access journals. Furthermore, the results will be presented at (inter)national conferences in the fields of end-of-life care, health services and general practice, and disseminated via the psychosocial care section of the DGP. Only data files that are lacking personally identifiable information will be maintained after the conclusion of the study. In accordance with the APA ethics code Sect. 8.14, “Sharing Research Data for Verification” [70], the project team will disseminate the results of the research in a timely manner and will not withhold unidentifiable data from other professionals seeking to verify the authors’ conclusions. Professionals seeking to use the data set for their own research must first gain permission from both the Institute for General Practice and Palliative Care at Hannover Medical School and the author(s). The Institute for General Practice and Palliative Care is well connected to the Medical Chamber of Lower Saxony (Ärztekammer Niedersachsen), the DGP, the DGP representation of Lower Saxony, the German Association of General Practitioners representation of Lower Saxony, Landesstützpunkt Hospizarbeit und Palliativversorgung Niedersachsen e.V. and Palliativstützpunkt Hannover. All of these parties will collaborate in the public dissemination, transfer and implementation of the project results, as established through former joint projects. Educational workshops for inpatient and community palliative care services will be organized to communicate the main project results. Finally, a report on the main results will be published on the website of the Institute for General Practice and Palliative Care and communicated in relevant working groups and to practitioners.

